### 2.6. Statistical Analysis

Continuous variables will be summarized as mean values ± standard deviations if normally distributed and compared with Student’s *t*-tests. Continuous variables will be summarized as median (interquartile ranges) if they are non-normally distributed and compared with Mann–Whitney U-tests. Dichotomous variables will be summarized as percentages and compared using Chi-squared tests. ANOVA tests will be performed to compare changes among the three subgroups. Box and whisker plots will be built to illustrate differences in OS and DNA damage biomarkers. Spearman and linear regression analyses will be performed to evaluate correlations and multivariate associations. Multivariate logistic regression analyses will be performed to evaluate determinants of γ-H2AX foci change. To examine whether the potential association of IR doses with γ-H2AX foci change is mediated by OS biomarkers, mediation analyses will be performed with the method described by Preacher and Hayes [61,62], which allows for testing the significance and magnitude of mediation. In all analyses, a two-sided significance level of *p* < 0.05 will be considered statistically significant. Data will be analyzed using IBM SPSS software version 29 (SPSS Inc., Chicago, IL, USA), STATA 18 (STATA Corp., College Station, TX, USA), and R version 4.3.1 (R Foundation for Statistical Computing, Vienna, Austria).

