### 2.2. Study Population and Recruitment

The study population comprises consecutive patients with health concerns related to the abdomen and pelvis organs and a clinical indication for contrast-enhanced (CE) abdomen and pelvis CT in the outpatient setting, with scheduled appointments at the Radiology Department of the University of Chile Clinical Hospital. Patients will be recruited via telephone call approximately 36–72 h before their appointment. Additionally, non-IR-exposed health-related personnel volunteers and their relatives without an indication of IR-associated examination will be recruited as a control group through a direct onsite invitation from the researchers.

Inclusion criteria: Male and female patients aged 18 to 75 capable of providing a signed informed consent.Exclusion criteria: Pregnant women, severe chronic kidney disease (glomerular filtration rate < 30 mL/min/1.73 m^2^), or contraindications for antioxidants supplementation or iodinated contrast examinations. Genetic syndromes, onco-hematologic diseases or history of peptic ulcers or urinary stones. Occupational exposure to IR; radiation therapy or chemotherapy in the last 6 months, or exposure to other IR-associated examinations in the previous 72 h or immediately after the abdomen and pelvis CT. Use CE CT premedication, antioxidant supplementation regularly or on the day of the CT exam, iron supplementation, or an iron-restricted diet.Sample size: proposed on the basis of other clinical studies to detect a significant reduction of increased DNA damage in the interventional group [50,51,52,53]. Assuming increases in γ-H2AX foci ranging 1–99% (~20% dispersion [59]), a sample size of *n* = 25 patients per group (assuming *n* = 3 missing values), there is an 80% power to detect any mean difference between the placebo and interventional groups > 16%.Study groups: Four groups, A_NONE-NONE_, B_NONE-EXP_, C_PLAC-EXP_ and D_VITC-EXP_, named according to corresponding intervention (none/placebo/vitamin C) and exposure (none/CE abdomen and pelvis CT), as detailed below. For reference on the study subjects’ protocol timeline, please also see Figure 3.

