A_NONE-NONE_: Not recipients of any intervention (placebo or vitamin C) nor exposure (CE abdomen and pelvis CT). Blood sample #1 (T_base_) will be collected 60–80 min before blood sample #2 (T_post_), with a clinical interview in between (T_ci_). B_NONE-EXP_: Not recipients of any intervention but exposed (T_exp_). Blood sample #2 (T_post_) will be collected 60–80 min after the blood sample #1, with a clinical interview (T_ci_) followed by the exposure (T_exp_) in between. Based on comparative data with A_NONE-NONE_ (i.e., interim estimates of the exposure effect), re-estimation of the starting sample size (*n* = 25) may be considered for these non-interventional groups [60]. With an estimation of the exposure effect, randomized placebo-controlled enrollment will start for the interventional (C_PLAC-EXP_/D_VITC-EXP_) groups.C_PLAC-EXP_: Recipients of a placebo (T_int_) and exposed (T_exp_). Blood sample #2 will be collected immediately prior to CT. Blood sample #3 (T_post_) will be collected 60–80 min after blood sample #1, with the administration of the placebo (T_int_), clinical interview (T_ci_) and exposure (T_exp_) in between.D_VITC-EXP_: Recipients of the oral vitamin C intervention (T_int_) and exposed (T_exp_). Blood sample #2 will be collected immediately prior to CT. Blood sample #3 (T_post_) will be collected 60–80 min after blood sample #1, with the administration of the vitamin intervention (T_int_), clinical interview (T_ci_) and exposure (T_exp_) in between.

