## 3. Discussion

This study is a limited, academic, randomized, placebo-controlled, four-arm clinical trial designed to evaluate the intervention consisting of an oral dose of vitamin C to counteract OS-mediated DNA damage in the scenario of exposure to IR-associated two-phase CE abdomen and pelvis CT.

The endpoints of the study are: (1) To compare the pre- and post-exposure change on OS and DNA-damage biomarkers in peripheral blood between exposed (not recipients of the oral vitamin C antioxidant intervention) and not exposed subjects (at an equivalent interval time); (2) To compare the pre- and post-exposure change on OS and DNA-damage biomarkers in peripheral blood among exposed patients, between recipients of a placebo, recipients of the oral vitamin C antioxidant intervention and not recipients of an intervention; (3) To estimate the mediating effect of IR-induced OS on DNA-damage biomarkers in peripheral blood of exposed subjects; and (4) To compare the total mediating effect of OS on IR-induced DNA damage among exposed subject, between recipients and not recipients of the oral vitamin C antioxidant intervention.

Beyond previous in vitro or mixed in vivo/in vitro studies [53], to the best of our knowledge, this is the first clinical outpatient study to be expressly designed to evaluate both (1) the preliminary assumption that OS plays a significant mediator role in IR-induced DNA damage; and (2) the hypothesis that enhancing the antioxidant capacity previous to exposure through an easy-to-use oral antioxidant intervention may counteract the associated IR-induced DNA damage through counterbalancing the OS-mediating effect on total DNA damage increase. 

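### The trial is sized on vitamin C versus placebo, but the test the plan gives for comparing changes is a three-group ANOVA that most naturally includes the non-randomised group B, so a significant F does not by itself show a vitamin C effect

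*Protocol article*

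**What the plan says.** **Who is randomised.** Section 2.3 allocates patients 1:1 at random to placebo (C) or vitamin C (D) and to no other group. Under section 2.2, group B has the CT but neither placebo nor vitamin C, and it lacks the extra blood draw that C and D have just before the scan. Groups A and B supply an estimate of the exposure effect, after which C and D open: "With an estimation of the exposure effect, randomized placebo-controlled enrollment will start for the interventional" groups.

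**What was sized.** Section 2.2 gives "a sample size of *n* = 25 patients per group (assuming *n* = 3 missing values") and says "there is an 80% power to detect any mean difference between the placebo and interventional groups > 16"%. This is a two-group statement about C and D.

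**What is compared.** The second endpoint, in the Discussion, compares biomarker change among exposed patients "between recipients of a placebo, recipients of the oral vitamin C antioxidant intervention and not recipients of an intervention", that is C, D and B. The fourth endpoint compares the mediating effect of oxidative stress between exposed subjects who took vitamin C and those who did not.

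**What is tested.** Section 2.6 says "ANOVA tests will be performed to compare changes among the three subgroups" and sets "a two-sided significance level of *p* < 0.05" throughout. It also lists t-tests and Mann–Whitney tests for continuous variables in general, without tying them to an endpoint or a pair of groups.

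**Label.** The Discussion calls the study a "randomized, placebo-controlled, four-arm clinical trial".

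**The concern.** The sample size and the analysis point at different comparisons. The sample size rests on D versus C, which randomisation and blinding protect. The only test tied to changes is an omnibus test that appears to include a cohort with neither protection.

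Group B can differ from C and D in enrolment period, assay run, case mix, the absence of a placebo drink, or the absence of the pre-CT draw. Any such difference in mean change feeds the F statistic just as a vitamin C effect would. If the three-group result were reported as the answer to the vitamin C question, the trial's central claim could rest on a non-randomised difference. The power stated in section 2.2 would also not be the power of the test performed.

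**Working it through.** **Inputs**

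- Two-sided alpha 0.05 (section 2.6).
- SD 20 percentage points, reading the dispersion in "Assuming increases in γ-H2AX foci ranging 1–99% (~20% dispersion [59"]) as the SD.
- Difference 16 points and n = 25 per group (section 2.2). I also use n = 22, because the text leaves open whether the 3 missing values come out of the 25.
- A shift in the mean change of group B. The documents give no value, so 5, 10 and 16 points are assumptions that show a range.

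**Step 1. Reproduce the plan's figure (C versus D)**

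n per group = 2(1.96 + 0.842)² × 20² / 16² = 24.5, rounded up to 25.

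The noncentrality of the t-test is 16 / (20√(2/25)) = 16 / 5.657 = 2.83. Power is 79.1% by the noncentral t and 80.7% by the normal approximation. The stated 80% is therefore a two-group calculation with 25 evaluable patients per arm. With 22 evaluable, power is 73.6% (t) or 75.6% (normal).

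**Step 2. Three-group F when vitamin C does nothing (C = D)**

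The noncentrality is λ = n Σ(μᵢ − μ̄)² / SD². With only B shifted by s, Σ(μᵢ − μ̄)² = (2/3)s². At n = 25 the degrees of freedom are 2 and 72.

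| Shift in B | λ | F rejects, n = 25 | C versus D t-test rejects |
|---|---|---|---|
| 0 | 0 | 5.0% | 5% |
| 5 | 25 × 16.67 / 400 = 1.04 | 13.3% | 5% |
| 10 | 25 × 66.67 / 400 = 4.17 | 41.5% | 5% |
| 16 | 25 × 170.67 / 400 = 10.67 | 82.5% | 5% |

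At n = 22 the 10-point shift gives 36.9%.

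**Step 3. What if a D versus C test follows a significant F?**

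I simulated this with SD 20, n = 25, no vitamin C effect and 100,000 replicates. Both F and the D versus C test are significant in about 2.5%, 3%, 4% and just under 5% of trials for B shifts of 0, 5, 10 and 16 points. The false claim rate for vitamin C stays at or below 5%.

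**Step 4. Power for a true 16-point difference between C and D**

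| Position of B | λ at n = 25 | F power, n = 25 | F power, n = 22 |
|---|---|---|---|
| Midway between C and D | 25 × (8² + 0 + 8²) / 400 = 8.00 | 69.8% | 63.6% |
| Equal to C | 25 × 170.67 / 400 = 10.67 | 82.5% | 76.8% |
| Direct C versus D t-test, for comparison | – | 79.1% | 73.6% |

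The F test loses power in the first case and gains a little in the second. Its power depends on where B falls, which the sample size calculation does not consider. Requiring a significant F before testing D versus C can only lower the power of that test, since both results must then be significant.

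**The case against.** The other side has a good case on several points.

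- **The subgroups are not named.** Reading them as B, C and D is an inference. It is a strong one, because the study has four groups and the second endpoint is the only one that lists three, but it is not stated. This stands.
- **A D versus C test is not excluded.** The sample size sentence identifies that contrast as the target, γ-H2AX is named as the primary outcome, and two-group tests are listed. A condensed article may leave follow-up comparisons to a fuller document. This stands as far as it goes. The article nonetheless states an endpoint and a test that do not match the contrast it sized.
- **The 13% and 41% are not type I error.** A reader might infer that the false positive rate for vitamin C is uncontrolled. The documents do not support that. When B is shifted, the hypothesis B = C = D is false and F rejects it correctly. A false vitamin C claim arises only if the omnibus result is itself read as a D versus C effect, which no section proposes, and step 3 shows that a follow-up test stays at or below 5%.
- **No shift in B is documented.** B, C and D share eligibility criteria and CT protocol, and the outcome is a within-person change, which removes stable baseline differences. Some overlap in enrolment is also possible, because the A and B sample sizes may be re-estimated. The shift sizes are therefore illustrative. B still starts earlier, is not randomised and gets no placebo.
- **Pooling B with C is not planned in so many words.** A reader might infer it from the fourth endpoint. The wording allows that grouping but does not state it, and the endpoint concerns a mediating effect rather than a mean difference.
- **B midway between C and D is only a scenario.** No section suggests it. The power loss is a possibility, not a forecast.
- **The four-arm description is a matter of labelling.** Sections 2.2 and 2.3 disclose what each group receives and who is randomised.

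**Conclusion.** The concern holds as a mismatch between the contrast that was randomised and sized and the comparison to which the plan attaches its test of changes. On the natural reading of the three subgroups, a significant F cannot on its own be taken as evidence for vitamin C. Under SD 20, 25 per group and no vitamin C effect, F rejects in 13% to 41% of trials for assumed shifts in B of 5 to 10 points, while the D versus C test stays at 5%. For a true 16-point effect, the power of F runs from about 70% (B midway) to 82% (B equal to C), against 79% for the direct test.

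The sample size itself is not in error for D versus C with 25 evaluable per arm. The finding does not show that the trial will be biased. It shows that the plan should say which comparison answers the vitamin C question.

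**What to change.** - In section 2.6 and in the endpoint list of the Discussion, name the change in γ-H2AX foci, D versus C, among randomised patients, two-sided 0.05, as the primary test of vitamin C. State that it does not depend on a significant three-group ANOVA.
- Name the three subgroups in the ANOVA sentence. Make all comparisons with B secondary and label them non-randomised.
- Define the fourth endpoint as D versus C.
- Describe the study as a two-arm randomised comparison with two non-randomised reference groups.

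The cost is wording only, with no added patients or assays, and the direct test is the one section 2.2 already sizes. The downside is that B no longer contributes to the primary vitamin C test, including the small power gain F would have if B behaved exactly like C.

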## 3. Discussion

This study is a limited, academic, randomized, placebo-controlled, four-arm clinical trial designed to evaluate the intervention consisting of an oral dose of vitamin C to counteract OS-mediated DNA damage in the scenario of exposure to IR-associated two-phase CE abdomen and pelvis CT.

The endpoints of the study are: (1) To compare the pre- and post-exposure change on OS and DNA-damage biomarkers in peripheral blood between exposed (not recipients of the oral vitamin C antioxidant intervention) and not exposed subjects (at an equivalent interval time); (2) To compare the pre- and post-exposure change on OS and DNA-damage biomarkers in peripheral blood among exposed patients, between recipients of a placebo, recipients of the oral vitamin C antioxidant intervention and not recipients of an intervention; (3) To estimate the mediating effect of IR-induced OS on DNA-damage biomarkers in peripheral blood of exposed subjects; and (4) To compare the total mediating effect of OS on IR-induced DNA damage among exposed subject, between recipients and not recipients of the oral vitamin C antioxidant intervention.

Beyond previous in vitro or mixed in vivo/in vitro studies [53], to the best of our knowledge, this is the first clinical outpatient study to be expressly designed to evaluate both (1) the preliminary assumption that OS plays a significant mediator role in IR-induced DNA damage; and (2) the hypothesis that enhancing the antioxidant capacity previous to exposure through an easy-to-use oral antioxidant intervention may counteract the associated IR-induced DNA damage through counterbalancing the OS-mediating effect on total DNA damage increase. 

Previous clinical studies [51,54] have investigated the hypothesis that an antioxidant intervention may counteract the IR-induced DNA damage without studying OS biomarkers to quantitatively size the mediating effect through this pathway, limiting further understanding of the underlying mechanisms and the overall potential of antioxidant intervention strategies. This is an important distinct methodological feature to aid in proposing further novel approaches. Compared to the study by Stehli et al. [51], which randomized patients to receive an intravenous antioxidant intervention, the current study aims to evaluate a simple oral intervention that may be used routinely in the outpatient setting, further making it unique in terms of its potential clinical impact. Also, the current study is centered on a clinical imaging examination with the most IR patient dose burden according to current international radiation dose estimation data, which is a strength compared to most previous studies in terms of the potential impact of its findings. Departing from a previous clinical outpatient study by Tao et al. [54], the current study proposes the use of patient dose estimates to allow for a comparison of its results with that of further studies on different IR-based clinical imaging examinations associated with stochastic effects in risk estimation fashion according to international recommendations. 

Furthermore, this is the first study to be performed in a multiple-group setting, with either exposure or no exposure, receiving either placebo, the antioxidant intervention or no intervention, each with appropriate statistical power, which is another strength of this study protocol to advance currently available literature. It should also be underscored that our measurements of baseline vitamin C will provide data for the first time to better characterize the clinical need for vitamin C supplementation to counterbalance IR-induced DNA damage. We also expect that the design and execution by a multidisciplinary team will allow a better understanding and more precise quantification of the role of OS mechanisms on the pathways that lead to IR-associated DNA damage, opening new avenues for potential counteracting effects by antioxidant interventions. 

The main limitations of our study are the use of a single CT protocol, a single antioxidant strategy, and a single-center design. Although current literature could not consistently support the hypothesis that a combination of antioxidants may provide an additive effect to vitamin C [52], whether a combination of antioxidants could offer better protection in particular clinical scenarios remains to be explored in further studies. We also acknowledge the use of a single DNA damage measurement method, whereas analyzing phosphorylation of ATM/ATR, p53, or cell death could provide a more detailed understanding and may be warranted in further studies. Lastly, while the current study is focused on the immediate effects of IR-induced OS mechanisms mediating DNA damage, the ultimate goal of advancing knowledge in this field is to provide the theoretical and evidence-based background that allows the study of potential long-term effects, e.g., whether the expected immediate effects may lower the risk of cancer among other, which remains as the follow-up research task to appropriately design with the results of the current study.

Computed tomography continues to be a matter of wide attention because of reports suggesting associated cancer risk, unexpected overexposures, over-utilization or inappropriate use, which heighten interest in making CT safer [63,64]. Reaction to these concerns has come from stakeholders, manufacturers, medical physicists, researchers and users, yet recent studies are again raising concerns related to these risks for a large number of patients [64,65]. Traditionally, the overuse of CT has often been attributed as the primary cause. However, recent data is derived from studies conducted in institutions with effective control mechanisms. In these settings, CT requests are filtered through a clinical decision support system, the typical CT doses are well below the national benchmark, and clinicians assess the CT indication appropriateness at outstanding high levels [64,65]. This study deals with the need expressed by the growing body of literature that leads to the conclusion that there is a need to increase awareness about potential opportunities focused on the opposing/receiving end of medical IR, particularly the defense system of patients against IR exposure. Further research is needed on novel intervention strategies to enhance the antioxidant capacity against IR-induced DNA damage. 

In conclusion, this is the first study designed to determine the mediating effects of IR-induced OS on DNA damage and the counteracting effect in recipients of an oral vitamin C intervention prior to IR exposure in the clinical scenario of outpatients undergoing two-phase CE abdomen and pelvis CT. Potentially favorable results of this study will generate the basis for larger clinical trials to further explore novel antioxidant strategies to counteract OS-mediated DNA damage in the scenario of exposure to IR-associated medical imaging examinations.

## Figures and Tables

**Figure 1 jcm-13-03866-f001:**
[figure not shown]
Classification of radiation, ionizing radiation, and examples including X-rays with its use in medical imaging.

**Figure 2 jcm-13-03866-f002:**
[figure not shown]
Direct (30–40%) and indirect effects (60–70%) of exposure to ionizing radiation lead to DNA damage.

**Figure 3 jcm-13-03866-f003:**
[figure not shown]
Study timeline. T_base_, baseline, informed consent signing and collection of blood sample #1, 60–80 min before collection of blood sample #2 (all groups). T_int_, intervention (groups C_PLAC-EXP_ and D_VITC-EXP_), 50–70 min before T_exp_. T_ci_, clinical interview, immediately after T_base_ (groups A_NONE-NONE_ and B_NONE-EXP_) or T_int_ (groups C_PLAC-EXP_ and D_VITC-EXP_). T_exp_, exposure, 60–80 min after Tbase (B_NONE-EXP_) or 50–70 min after T_base_ (group B_NONE-EXP_) or after T_int_ (groups C_PLAC-EXP_ and D_VITC-EXP_), with the collection of blood sample #2 immediately prior to CT for groups C_PLAC-EXP_ and D_VITC-EXP_. T_post_, post-intervention-like schedule, collection of blood sample #2 (groups A_NONE-NONE_ and B_NONE-EXP_) or #3 (groups C_PLAC-EXP_ and D_VITC-EXP_), 60–80 min after T_base_, ~1–5 min after T_exp_ for groups B_NONE-EXP_, C_PLAC-EXP_ and D_VITC-EXP_.

**Table 1 jcm-13-03866-t001:** CT scanning parameters.

Parameters	Non-Contrast Phase	Contrast-Enhanced Phase
kV (reference)	100	100
mAs (reference)	180	180
Dose optimization level	3	7
Rotation time (s)	0.5	0.5
Delay (s)	2	80
Pitch	1	1
Collimator (mm)	128 × 0.6	128 × 0.6

